#### Secondary analyses

We will also analyse the mean values of the secondary continuous outcomes (other domains of FHSQ, PSEQ and physical activity level) using linear mixed models. The risk difference ($$ =\frac{Positive\ outcomes\ in\  one\  group}{Number\ of\ participants\ in\ group} $$ - $$ \frac{Positive\ outcomes\ in\ another\ group}{Number\ of\ participants\ in\ group} $$) will be calculated for the dichotomised GROC to determine the probability of being improved, for the PASS (yes/no) to determine the probability of achieving a self-evaluated satisfactory result within the 12, 26 and 52 weeks of intervention. We will also calculate risk differences to determine the probability of experiencing a deterioration of PF, defined as a decrease in FHSQ pain ≥ 14.1 points from one follow-up to another or changing one’s status from having achieved PASS to no longer having achieved PASS. We will calculate the number needed to treat for the primary outcome at the primary endpoint as 1/risk difference. We will use a Kaplan-Meier survival analysis and compare survival curves using log-rank tests to investigate between-group differences in time to achieving PASS [55, 56]. If a participant changes PASS multiple times (e.g., achieving PASS before 12 weeks, reporting not to have achieved PASS at 26 weeks and then having achieved PASS again at the 52-week follow-up), only time to the first PASS achieved is used in the analysis.

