A systematic review and network meta-analysis compared several commonly used treatment options for PF [18]. Overall, they concluded that none of the investigated treatments were superior to the others, but different treatments may have different temporal profiles. Some are efficacious in the short term (< 4 weeks), such as an injection with corticosteroid, whereas others (e.g., exercises or orthoses are more efficacious in the longer term [> 12 weeks]) [18–22]. Heavy-slow resistance training (HSR) was not included in the review, but it is generally known for a long-term efficacy in the rehabilitation of both upper- and lower-limb tendinopathies [23–25]. In PF, HSR has been found to be superior to plantar fascia-specific stretching, but only 6% achieve an acceptable symptom state within 12 weeks [16, 26]. This emphasises the need for additional improvements to current care of these patients.

Combining HSR with a corticosteroid injection may provide both short- and long-term pain relief for individuals with PF. We recently conducted a feasibility study of the combination of these two treatments, which supports running an efficacy trial. Patients’ rating of acceptability, time to commencement of exercise after the injection, compliance with exercise, recruitment rate, and changes in foot-related health and function over time supported this current proposed trial [27]. In theory, combined treatments could supplement each other and give both an immediate and long-term pain reduction.

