### Sample size

The minimal clinically important difference of the FHSQ pain domain has been found to be either 12.5 or 14.1 points in this patient population [37, 52]. We have chosen the most conservative option (i.e., 14.1 points) to form the basis of the sample size calculation. Based on a standard deviation of 22 points, which is comparable to the overall standard deviations found in previous studies of this patient population [19, 53, 54], a two-sided 5% significance level, and a power of 90%, a sample size of 53 participants in each group will be necessary. Taking into consideration possible drop-outs, we will include 60 participants in each group, and thus the total sample size will be 180 participants.

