#### Primary analysis

The primary analysis will investigate the between-group difference in FHSQ pain. We will use a linear mixed effects model with the participant as a random effect, and time (4, 12, 26 and 52 weeks), group allocation (PA or PAX or PAXI) and baseline value as fixed effects. Conclusions will only be drawn on the basis of the primary endpoint (12 weeks).

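### PASS and GROC are to be compared by crude risk differences; adjusting for baseline FHSQ pain would probably give a small gain in precision, mainly for PASS

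*Protocol article*

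**What the plan says.** Under Secondary analyses, the article prints the formula for the risk difference: the number with a positive result divided by the size of the arm, minus the same fraction in the comparator arm. This difference "will be calculated for the dichotomised GROC to determine the probability of being improved, for the PASS (yes/no"). PASS is assessed as achieved by 12, 26 and 52 weeks. No covariate enters the formula, and the comparison of time to PASS (Kaplan-Meier, log-rank) names none either.

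Under Primary analysis, the mixed model for FHSQ pain has time, "group allocation (PA or PAX or PAXI) and baseline value as fixed effects". The same section restricts conclusions to the 12-week primary endpoint.

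Under Randomisation and blinding, sex is the only stratification factor. Under Statistical analyses, the article refers to a separate analysis plan, which is not available here, and says that missing outcomes will be multiply imputed.

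The only PASS rate in the article is in the Background, from earlier work on heavy-slow resistance training: "only 6% achieve an acceptable symptom state within 12 weeks".

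**The concern.** Baseline pain is not balanced by design and is recorded for everyone. The trial already treats it as prognostic for its main outcome. PASS asks whether the participant is satisfied and needs no further treatment, so those who start with less pain can reasonably be expected to reach it more often. A comparison that ignores baseline then carries avoidable noise.

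At stake is the width of the intervals for the proportions satisfied and improved, which are wide with 60 per arm. A chance baseline difference would also be removed from the pain comparison but not from the PASS comparison in the same patients. If adjustment is added only after such a difference has been seen, it will look selective, which is the reason to settle it in advance.

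**Working it through.** **The plan's own figure.** The only sample-size figure concerns FHSQ pain; none is given for PASS or GROC. Inputs from Sample size are, for the target difference, "We have chosen the most conservative option (i.e., 14.1 points) to form the basis of the sample size calculation"; for the spread of scores, "Based on a standard deviation of 22 points"; and for the error rates, "a two-sided 5% significance level, and a power of 90" per cent. The normal approximation gives 2 × (1.960 + 1.282)² × (22/14.1)² = 51.2, so 52 per arm. The two-sample t-test gives 52.14, rounded up to 53. This agrees with the statement that "a sample size of 53 participants in each group will be necessary". After the drop-out allowance, "we will include 60 participants in each group, and thus the total sample size will be 180 participants", so 60 per arm is used below.

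**Crude precision.** The standard error of the crude risk difference is √(2p(1−p)/60), with the same p in both arms. At p = 0.50 it is 9.1 percentage points, a 95% half-width of 1.96 × 9.1 = 17.9 points. At p = 0.06 the half-width is 8.5 points.

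**Effect of adjustment.** Let r be the within-arm correlation between baseline pain and the 0/1 outcome. The adjusted variance is about (1 − r²) times the crude variance. Assumption: the latent trait behind the outcome correlates ρ = 0.3 to 0.5 with baseline pain. Then r = ρ × φ(z)/√(p(1−p)), where z is the normal quantile at p. The multiplier φ(z)/√(p(1−p)) is 0.399/0.500 = 0.798 at 50%, 0.386/0.490 = 0.789 at 40%, 0.280/0.400 = 0.700 at 20% and 0.119/0.237 = 0.502 at 6%.

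**Chance imbalance.** The difference in baseline means between two arms of 60 has a standard deviation of √(2/60) = 0.183 baseline SDs. An imbalance of that size moves the crude risk difference by 0.183 × r × √(p(1−p)).

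| Response | r for ρ 0.3–0.5 | Variance cut | SE cut | 95% half-width, crude → adjusted (points) | Shift from one-SE imbalance (points) |
|---|---|---|---|---|---|
| 50% | 0.24–0.40 | 6–16% | 3–8% | 17.9 → 17.4–16.4 | 2.2–3.6 |
| 40% | 0.24–0.39 | 6–16% | 3–8% | 17.5 → 17.0–16.1 | 2.1–3.5 |
| 20% | 0.21–0.35 | 4–12% | 2–6% | 14.3 → 14.0–13.4 | 1.5–2.6 |
| 6% | 0.15–0.25 | 2–6% | 1–3% | 8.5 → 8.4–8.2 | 0.7–1.1 |

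The variance cut at 40 to 50% response is worth about 6 to 19% more participants (1/(1 − r²) − 1).

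**Weaker correlations.** If the observed r is 0.1, the standard error ratio √(1 − r²) is 0.995; at 0.2 it is 0.980. The gain is then 2% or less.

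**Check by simulation.** Trials of 60 versus 60 at about 30% versus 50% response were simulated (3,000 per setting), with logistic regression on baseline standardised to a marginal risk difference. The ratio of adjusted to crude standard deviation was 1.002 at r = 0, 0.983 at 0.18, 0.958 at 0.30 and 0.919 at 0.40, close to √(1 − r²). Mean crude and adjusted differences agreed within 0.12 percentage points. Illustrative power for 30% versus 50% is 61% crude, 65% at r = 0.3 and 69% at r = 0.4.

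**The case against.** The strongest reply is that nothing here is wrong. A difference of raw proportions is a legitimate estimator in a randomised trial. A reader might infer from the contrast with the primary model that the crude differences are biased, or that a baseline imbalance would invalidate them. Neither follows: the simulated means agree, and the crude interval already allows for chance imbalance. A one-standard-error imbalance moves the estimate by at most about 3.6 points at 50% response, against a crude standard error of 9.1. This part of the objection stands in full.

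Second, the size of the gain rests on a correlation that the documents do not supply. Entry requires mean heel pain of at least 30 mm, which narrows the baseline range and may weaken the correlation. That stands, so the loss of precision is likely rather than established.

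Third, the mechanism fits PASS and not GROC. GROC rates change; more baseline pain may leave more room to improve or may predict a poorer course. PASS is also partly something achieved within a period rather than a state on a given day, though the argument from starting pain still applies. The restriction to PASS stands.

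Fourth, these are secondary outcomes, conclusions are tied to the 12-week primary endpoint, and the unseen analysis plan may already adjust. The first two parts limit the consequence. The last does not remove the point, because the article prints a specific crude formula rather than leaving the estimator open; if the plan adjusts, the two texts should be aligned.

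**Conclusion.** The point holds as a minor efficiency improvement to secondary analyses. The stated estimator for PASS and GROC is crude, although a baseline score already collected, used in the primary model and not a stratification factor could be brought in at almost no cost. Under an assumed latent correlation of 0.3 to 0.5, the standard error would fall by about 3 to 8% at 40 to 50% response, 2 to 6% at 20% and 1 to 3% at 6%. If the observed correlation is 0.2 or less, the gain is negligible. The case is reasonable for PASS and uncertain for GROC. The documents do not support reading this as bias, as an internal contradiction, or as a threat to the trial's conclusions.

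**What to change.** Keep the risk difference as the effect measure. Pre-specify an estimate adjusted for baseline FHSQ pain, and for sex as the stratification factor where events allow. Either logistic regression with marginal standardisation or a linear model of the 0/1 outcome with robust standard errors will do, fitted within each imputed data set and then combined. Report the crude difference beside it.

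State a fallback as well. At the 6% PASS rate in the Background, 60 × 0.06 = 3.6, so only three or four events per arm might be seen at 12 weeks. With so few events, limit adjustment to one covariate, or report the crude difference alone with a score interval.

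The cost is a sentence or two in the analysis plan and a few lines of code. No new data and no change in sample size are needed. The plan is due to be published before the last inclusion, so that is the natural place for it.

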#### Cost-effectiveness analysis

The reporting of the economic evaluation will follow the Consolidated Health Economic Evaluation Reporting Standards checklist for a more transparent and complete reporting of methods and findings [57]. For each intervention, mean values (and standard errors of the mean) will be reported for the main categories of estimated costs and QALYs, as well as mean differences between the comparator groups. Probabilistic sensitivity analyses will be used to estimate the decision uncertainty and calculate incremental cost-effectiveness ratios.

### Data monitoring and quality assurance

All data will be stored electronically and are handled according to the General Data Protection Regulation. Data safety may be overseen unannounced by the Danish Data Protection Agency. Participant data will be stored in REDCap, whereas data processor agreements, collaboration agreements between the project group and general practices and protocols will be stored on a secure server at Aalborg University. To prevent data entry errors, data collection instruments have been developed in REDCap so that required data must be included or an error will be displayed, and validation of each field has been chosen (e.g., if the format of the data does not appear to be a date in the field ‘Date’, an error is displayed). Data are checked once per week by the project manager to ensure there are no missing data. All data will be kept for 10 years after completion of the trial in accordance with the European Code of Conduct for Research Integrity.

## Discussion

### Future implications

PF is a condition with a wide variety of different treatment options available, with no single treatment showing superiority [18, 51]. HSR is increasingly being used for rehabilitation of PF, despite its effects having only been compared with stretching in a single study [26]. Our recent research with HSR for PF shows within-group improvements in pain similar to those of studies investigating foot orthoses, corticosteroid injections and even placebo injections [16]. By comparing HSR with no HSR and a heel cup and patient advice only, we will be able to answer if performing exercises is worth the extra time and effort required from the patient.

Corticosteroid injection may reduce heel pain for up to 1 month, and adverse events are generally rare and have been reported not to occur when the injection was performed under ultrasound guidance [19–21]. After 1 month, the improvement in symptoms is similar to that of placebo. In contrast, the effects of HSR are known for taking some time to manifest, and performing HSR is usually painful [16, 17, 26]. Patients ask for both short-term and long-term pain reduction, and the combination of these two treatments may potentially offer this. Moreover, in the qualitative data from our feasibility study, we found that several participants felt that pain during exercise was reduced due to the pain relief associated with the injection [27]. This may improve exercise compliance and overall improvement. Despite our hypothesis of superiority of combining the injection with HSR, an injection with corticosteroid may potentially reduce the effect of HSR. This would be similar to how corticosteroids reduced the effect of physiotherapy in a former trial in patients with lateral elbow tendinopathy. In that trial, corticosteroid injections and physiotherapy led to a lower rate of successful outcomes than placebo injections and physiotherapy after 1 year [24]. This indicates that corticosteroids decreased the effect of physiotherapy. Furthermore, the combination of exercise and an injection was not superior to an injection alone in patients with subacromial pain syndrome [29]. One concern is that the pain reduction following the injection will hamper exercise compliance and affect long-term outcomes negatively.

The implementation of our findings will be aided by the inclusion of a cost-effectiveness analysis. There are obvious differences between treatments in how much time and materials are required. The treatment offered in the PA group requires the least, whereas the PAXI group requires the most. However, this difference may be equalised by the potential savings on a societal level in terms of sick leave or on a personal level in terms of QALYs, condition-related improvement and personal expenses. Any future implementation will also be dependent on the patients’ experiences and expectations, which is why patients are involved in the interpretation of the trial findings.

Recruiting patients for trials in primary care is a large challenge, and less than one-third of trials recruit patients within the original recruitment time frame [58]. We use an adaptive recruitment strategy in which we focus primarily on recruitment from general practices, but we will use Facebook recruitment to ensure that the timeline is kept. We may increase the number of recruiting practices or the area and the money used for sponsoring Facebook posts, depending on recruitment rate. This may help inform effective ways of recruiting a large number of participants from general practice in studies requiring large numbers of patients.

### Strengths

First, the involvement of patients and GPs in developing the patient advice intervention enables a high level of acceptability for users. Second, all of the interventions are within scope, knowledge and skill levels of primary care clinicians and practices, so they will have a high feasibility of being implemented, regardless of trial findings. Third, all potential outcomes of the trial may influence future clinical practice. If no superiority of one intervention is found over the others, the minimally invasive or the most cost-effective should be implemented, depending on patient preferences. Fourth, to minimise bias, the data analysis will occur blind to group allocation and will be performed according to a pre-established and publicly accessible analysis plan.

### Limitations

First, despite the trial being rooted in general practice, the treatments are delivered at the hospital and at a private rheumatology clinic for logistical reasons by physiotherapists and a rheumatologist. Second, if the PAXI group is superior to the others, we cannot disregard that some of that superiority will derive from the placebo effect of receiving an injection. However, we evaluated how the relevance of adding a placebo injection to the PAX group had lessened in light of research concluding the superiority of corticosteroid injections compared with placebo [19–21]. Third, we recruit from both general practice and from Facebook, and we do not know if these recruitment sources yield the same type of patient; still, based on our previous study where we recruited patients solely via Facebook, three in four will have seen their GP due to their PF [17]. This may increase the generalisability of the patients recruited from Facebook to those seen in general practice.

### Trial status

Recruitment was started on January 21, 2019, and the first participant was included on February 7, 2019. No amendments have been made to the protocol (version 2.0 January 14, 2019) since it was pre-registered with ClinicalTrials.gov. When this protocol was submitted for publication (October 5, 2019), a total of 96 participants had been included in the trial. We expect recruitment to be completed in July 2020.

## Data Availability

Data will be made available upon reasonable request.

## Abbreviations

FHSQ: Foot Health Status Questionnaire
GP: General practitioner
GROC: Global Rating of Change
HSR: Heavy-slow resistance training
MET: Metabolic equivalent
PA: Patient advice and heel cup
PASS: Patient Acceptable Symptom State
PAX: Patient advice, heel cup and heavy-slow resistance training
PAXI: Patient advice, heel cup, heavy-slow resistance training and corticosteroid injection
PF: Plantar fasciopathy
PSEQ: Pain Self-Efficacy Questionnaire
QALY: Quality-adjusted life-year
RM: Repetition maximum
SPIRIT: Standard Protocol Items: Recommendations for Interventional Trials
TiDieR: Template for Intervention Description and Replication checklist and guide
VAS: Visual analogue scale
